#### Intervention period

##### Experimental group

Caregivers in the experimental group will participate in the 6-week intervention ‘Partner in Sight’ and collect ESM data for three consecutive days a week. Every two weeks they will receive ESM-derived feedback in a face-to-face session with a coach in their home or at the MUMC+ according to their preference. This sums up to a total of three feedback sessions. The aim of the feedback sessions is to provide an overview of the caregiver’s everyday functioning, including their mood (i.e. levels of positive affect), daily life activities, and social interactions. The focus will be on positive rather than negative emotional experiences and how these relate to specific daily contexts. In this way, we try stimulate caregivers to redirect their behavior towards situations that elicit positive emotions.

At the beginning of each feedback session average levels of positive affect experienced during the past two weeks will be presented. Subsequently, a feedback module on *daily activities* and/or *social interactions in daily life* will be discussed with the caregiver. Feedback modules are based on an existing ESM intervention, which has proven to be effective in people with depression [9]. During the first feedback session the module ‘*daily activities’* will be discussed with the caregiver. The data may, for example, illustrate that positive emotions increase during moments of active relaxation, while the caregiver is actually spending the least amount of time on active relaxation activities. The coach will stimulate caregivers to think about the findings and to implement new insights into their daily lives. In the second feedback session the module ‘*social interactions in daily life’* will be added. A caregiver might state, for example, that he prefers to spend his time alone, without any company. The feedback, however, may show that positive emotions are experienced particularly while being in company instead of when being alone. This finding might induce an increase in social interactions, which in turn may lead to increased positive emotions. The third session will combine both modules. At the end of each session the weekly progress in levels of positive affect yielded by daily activities and/or social interactions will be evaluated. A more detailed description of the feedback modules is presented in Table 1.

**Table 1 Tab1:** Feedback modules of the intervention ‘Partner in Sight’

Session	Feedback Module	Description
1	1 Daily activities	- Pie chart of the average time spent on different activities (e.g. caring for partner, household, active relaxation, passive relaxation, resting, self care) during the past two weeks
		- Graph demonstrating the relationship between different kind of activities and experienced levels of positive affect
		- Pie chart of the average time spent on active relaxation in the presence and absence of the PwD
		- Graph showing experienced levels of positive affect during active relaxation in the presence and absence of the PwD
		- Pie chart of the average time spent on passive relaxation in the presence and absence of the PwD
		- Graph showing experienced levels of positive affect during passive relaxation in the presence and absence of the PwD
2	1 & 2 Social interactions	Added:
		- Pie chart of the average time spent in different kinds of company (e.g. partner, friends, family, colleagues, alone) during the past two weeks
		- Graph demonstrating the relationship between different types of social company and experienced levels of positive affect
3	1 & 2	See description above
1,2,3	General graphs	- Graph including information on average levels of positive affect during the past two weeks
		- Graph demonstrating the weekly progress in levels of positive affect during the course of the intervention
		- Graph demonstrating the weekly progress in levels of positive affect yielded by daily activities
		- Graph demonstrating the weekly progress in levels of positive affect yielded by social interactions

*PwD* person with dementia

The coach will present all feedback verbally and graphically (in clear pie charts and bar graphs) to the caregiver according to a standardized protocol. Before the start of the study all coaches will receive training with clear instructions on how to provide feedback. After each session both the caregiver as well as the involved clinician or care counselor will be provided with a written copy of the feedback.

At the end of each feedback session there will be a debriefing concerning the use of the PsyMate, e.g. difficulties operating the device, technical problems, items that are unclear, and reasons for missing measurements. Furthermore, the participant will be reminded and encouraged to fill out the PsyMate during the following two weeks as accurately as possible conform the instructions given by the coach. During the third feedback session the coach will additionally conduct an unstructured interview to assess the feasibility of the intervention.

##### Pseudo-experimental group

A pseudo-experimental group is added to the study design to investigate whether the ESM-derived feedback adds value to the use of the PsyMate without receiving any direct feedback. Repeated self-assessments might already increase caregivers’ self-awareness and redirect their behavior accordingly [21].

Caregivers in the pseudo-experimental group will participate in a 6-week pseudo-intervention and collect ESM data for three days a week. Every two weeks they will receive a face-to-face session with a coach. However, during these sessions they will not be provided with feedback on their daily recordings. Alternatively, a semi-structured interview on their well-being during the past two weeks will be performed to prevent any effects of different duration of contact with the coach.

At the end of each session caregivers will, similar to the participants in the experimental group, be provided with a debriefing concerning the use of the ESM-device.

##### Control group

Caregivers in the control group will receive care as usual during the 6-week intervention period. Care conditions will differ among caregivers and will be registered carefully at baseline. In general, care as usual includes low-frequent sessions with a clinician from the memory clinic or counselor from a caregiver support service.

#### Post-intervention assessment (T1)

After the intervention period a post-intervention assessment will be executed in the caregiver’s home or at the MUMC+ according to their preference. As part of the post-intervention assessment, caregivers will be asked to participate in a 3-day ESM post measurement. They will be shortly briefed with respect to the procedure. Afterwards, all participants will be asked to complete a questionnaire concerning their general experiences with the ESM-device during the complete study period. Based on their answers a semi-structured interview will be conducted to discuss the questionnaire. Finally, caregivers will be asked again to complete a number of retrospective questionnaires at their own convenience as part of the effect evaluation.

#### Follow-up assessments (T2 & T3)

A two- and six-month follow-up assessment will be administered in which participants receive a number of retrospective questionnaires by post and are asked to return them after completion.

### Retention

Participants will be provided with periodic newsletters to inform them about the current status of the study, plans for the next phase, as well as to acknowledge their support.

### Instruments

For an overview of the instruments used during the baseline, post-intervention and follow-up assessments see Table 2.

**Table 2 Tab2:** Flowchart of measures used during the assessments

	Pre-test	Intervention period			Post-tests		
	T = 0	FB1	FB2	FB3	T = 1	T = 2	T = 3
Primary outcome measures RCT							
- Sense of competence: SSCQ	X				X	X	X
- Perceived control: PMS	X				X	X	X
Secondary outcome measures RCT							
- Depressive symptoms: CES-D	X				X	X	X
- Perceived stress: PSS	X				X	X	X
- Anxiety symptoms: HADS-A	X				X	X	X
ESM outcome measures RCT							
- Momentary positive affect	X				X		
- Momentary negative affect	X				X		
Additional measures RCT							
- Demographic variables	X						
- Neuropsychiatric symptoms in PwD: NPI-Q	X				X	X	X
- Quality of the relationship: 4 items of the University of Southern California Longitudinal Study of Three-Generation Families measures of positive affect	X				X	X	X
- Coping: UCL	X				X	X	X
- Personality: subscale neuroticism of NEO-FFI	X				X	X	X
Outcome measures process evaluation							
- Subjective experiences with intervention: quantitative questionnaire & qualitative semi-structured interview				X			
- Subjective experiences with the use of the ESM device: quantitative questionnaire					X		
- Subjective experiences with ESM procedure: quantitative questionnaire		X	X	X	X		
Outcome measures economic evaluation							
- Resource use: RUD-lite	X				X	X	X
- Quality of life: EQ-5D	X				X	X	X

*RCT* randomized controlled trial, *SSCQ* Short Sense of Competence Questionnaire, *PMS* Pearlin Mastery Scale, *CES-D* Center for Epidemiological Studies Depression Scale, *PSS* Perceived Stress Scale, *HADS-A* Hospital Anxiety and Depression Scale, Anxiety subscale, *PwD* person with dementia, *NPI-Q* Neuropsychiatric Inventory Questionnaire, *UCL* Utrechtse Coping List, *NEO-FFI* NEO Five-Factor Inventory, *ESM* Experience Sampling Methodology, *RUD-lite* Resource Utilization in Dementia – shortened version, *EQ-5D* EuroQoL-5D

#### Primary outcome measures

*Sense of Competence*: caregivers’ subjective feelings of competence will be assessed with the Short Sense of Competence Questionnaire (SSCQ), a shortened version of the 27-item Sense of Competence Questionnaire (SSQ) [28]. The SSCQ consists of seven items, rated on a 5-point scale from 1 (agree very strongly) to 5 (disagree very strongly). The items reflect three domains of caregivers’ feelings of being capable to care for the PwD: satisfaction with their own performance as a caregiver (2 items), satisfaction with the PwD as a care recipient (3 items), and consequences of involvement in care for personal life of the caregiver (2 items). A total sum score (range 7–35) will be calculated for each participant. Higher sum scores represent higher levels of sense of competence. The scale displays good content and construct validity in previous research [28].

*Perceived control:* the extent to which a person perceives him- or herself to be in control of events and on-going situations, also known as mastery, will be measured with the Pearlin Mastery Scale (PMS) [29]. The scale contains seven items with scores varying from 0 (completely agree) to 4 (completely disagree). Items are summed to form a total mastery score (range 0–28), with higher scores indicating greater perceived control. The psychometric properties of the PMS are good according to previous research [30].

#### Secondary outcome measures

*Depressive symptoms:* the Center for Epidemiological Studies Depression Scale (CES-D) will be used to assess depressive symptoms among caregivers [31]. It includes twenty items that rate the frequency of symptoms during the past week. Item scores range from 0 (rarely or none of the time present [less than 1 day]) to 3 (most or all of the time present [5–7 days]). The total sum score ranges from 0 to 60, with higher scores indicating more depressive symptoms. Items depict major components of depressive symptomatology, such as depressed mood, feelings of guilt and worthlessness, feelings of helplessness and hopelessness, psychomotor retardation, loss of appetite, and sleep disturbance. The CES-D has been widely used in research on caregiving and has proven to be sensitive to changes in caregiver depressive symptoms after intervention [14].

*Perceived stress:* the Perceived Stress Scale (PSS) will be used to measure the degree to which situations in one’s life are appraised as stressful [32]. The PSS consists of ten items, rated on a 5-point scale from 0 (never) to 4 (very often), regarding unpredictability, control, and overload. Total sum scores on the PSS range from 0 to 40, with higher scores representing higher levels of stress. Adequate validity and reliability has been demonstrated in previous research [32].

*Anxiety symptoms:* the 7-item anxiety subscale of the Hospital Anxiety and Depression Scale (HADS) will be employed to assess the severity of anxiety symptoms in caregivers [33]. Item scores range from 0 (not at all) to 3 (a great deal of the time) and will be accumulated to produce a total sum score (range 0–21), with higher scores indicating more anxiety. The HADS has frequently been used in caregivers of PwD and has shown good reliability rates [34].

#### ESM outcome measures

*Momentary positive and negative affect:* the ESM data collected during the 3-day ESM baseline measurement and 3-day ESM post measurement will be used to assess caregivers’ momentary positive and negative affect. Positive affect will be defined as the mean score of the items: ‘I feel cheerful’, ‘I feel relaxed’, ‘I feel enthusiastic’, and ‘I feel satisfied’. Negative affect will be defined as the mean score of the items ‘I feel insecure’, ‘I feel lonely’, ‘I feel anxious’, ‘I feel irritated’, ‘I feel down’, ‘I feel desperate’, ‘I feel tensed’, and ‘I feel confident’. A mean positive and negative affect score will be calculated for each completed beep during the day, with higher scores indicating higher levels of positive and negative affect.

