### Study aims

The specific objectives of the current study are:*Process evaluation* to investigate the internal and external validity of the intervention based on sampling quality (recruitment, randomization, and reach) and intervention quality (relevance, feasibility, and performance according to protocol). The process evaluation will be conducted prior to the effect evaluation in order to provide essential information about credibility and generalizability [24].*Effect evaluation* to assess whether ‘Partner in Sight’ is superior to a pseudo-intervention and control group in terms of producing a clinically significant increase in subjective well-being, as proven by an increase in caregivers’ sense of competence, perceived control, momentary positive affect, and a decrease in psychological complaints (depression, anxiety, stress, and momentary negative affect). A follow-up evaluation will be conducted to examine whether the effects have lasted two and six months after the intervention.*Economic evaluation* to assess the cost-effectiveness of ‘Partner in Sight’ by estimating the impact of the intervention on resource use, costs, and health outcomes.

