After each beep, caregivers will be asked to complete a questionnaire presented on the screen of the PsyMate, including current affect (four positive affect and eight negative affect items), self-esteem (four items), physical well-being (four items), as well as current context and activities (daily life activities, social company, location and events). At the end of each questionnaire, caregivers will have to indicate whether the beep disturbed them. Answering all questions will take approximately three minutes per beep ([name] et al.: Dealing with daily challenges in dementia (Deal-id study): an innovative approach to assess caregiver functioning in the flow of daily life, submitted). Additionally, the PsyMate will be programmed to generate a morning and evening questionnaire at the beginning and end of each day. The morning questionnaire consists of six items regarding their sleep quality during the previous night and their current level of energy. The evening questionnaire contains twenty-five items concerning the caregivers’ daily sense of well-being and competence, and neuropsychiatric symptoms in the PwD during that day. Responses will be rated on 7-point Likert scales (ranging from 1 ‘not at all’ to 7 ‘very much’), bipolar scales (ranging from −3 ‘very unpleasant/very unimportant’ to +3 ‘very pleasant/very important’), a Visual Analogue Scale (ranging from 0 ‘worst imaginable health’ to 100 ‘best imaginable health’), and box-checking formats. Responses cannot be corrected afterwards. An overview of the ESM items with corresponding response choices and concepts is presented in the Appendix. The specific items of the ESM questionnaires were developed and selected according to information available from previous ESM studies [25, 26], knowledge about the experiences and situations that caregivers of PwD could be expected to encounter in daily life, and the guidelines for item development created by ESM experts [27]. Moreover, the ESM questionnaires were recently tested in a feasibility study that yielded positive results ([name] et al.: Dealing with daily challenges in dementia (Deal-id study): an innovative approach to assess caregiver functioning in the flow of daily life, submitted).

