#### ESM outcome measures

Subjects have to complete at least 33 % of the ESM beeps in order to be included in the ESM data analysis [4]. To investigate changes in momentary positive and negative affect between the 3-day ESM baseline and post measurement for each group, an LMM will be performed for both outcome measures. LMMs are ideally suited for ESM data, since these models take into account the hierarchical data structure in which multiple ESM observations (beep level 1) are nested within days (day level 2), and days are nested within subjects (subject level 3). The XTMIXED command in STATA 12.1 [49] will be used to conduct analyses with group (3 levels: experimental, pseudo-experimental, and control group), time (2 levels: baseline and post-intervention), and the two-way interaction between group and time as fixed factors. Random slopes, representing positive or negative affect, will be added at the subject, day, and beep level. Potential confounders will be included in the model as covariates.

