## Appendix

**Table 3 Tab3:** Description of the ESM concepts, items and response choices in the daily, morning and evening questionnaire

Daily questionnaire		
Concept	Item	Rating scale
Positive affect	1. I feel cheerful	7-point scale (1 ‘not at all’ to 7 ‘very much’)
	2. I feel relaxed	7-point scale (1 ‘not at all’ to 7 ‘very much’)
	3. I feel enthusiastic	7-point scale (1 ‘not at all’ to 7 ‘very much’)
	4. I feel satisfied	7-point scale (1 ‘not at all’ to 7 ‘very much’)
Negative affect	5. I feel insecure	7-point scale (1 ‘not at all’ to 7 ‘very much’)
	6. I feel lonely	7-point scale (1 ‘not at all’ to 7 ‘very much’)
	7. I feel anxious	7-point scale (1 ‘not at all’ to 7 ‘very much’)
	8. I feel irritated	7-point scale (1 ‘not at all’ to 7 ‘very much’)
	9. I feel down	7-point scale (1 ‘not at all’ to 7 ‘very much’)
	10. I feel desperate	7-point scale (1 ‘not at all’ to 7 ‘very much’)
	11. I feel confident	7-point scale (1 ‘not at all’ to 7 ‘very much’)
	12. I feel tensed	-point scale (1 ‘not at all’ to 7 ‘very much’)
Self-esteem	13. I like myself	7-point scale (1 ‘not at all’ to 7 ‘very much’)
	14. I am ashamed of myself	7-point scale (1 ‘not at all’ to 7 ‘very much’)
	15. I doubt myself	7-point scale (1 ‘not at all’ to 7 ‘very much’)
	16. I am satisfied with myself	7-point scale (1 ‘not at all’ to 7 ‘very much’)
Physical well-being	17. I am tired	7-point scale (1 ‘not at all’ to 7 ‘very much’)
	18. I feel well	7-point scale (1 ‘not at all’ to 7 ‘very much’)
	19. I am in pain	7-point scale (1 ‘not at all’ to 7 ‘very much’)
	20. I have problems in walking	7-point scale (1 ‘not at all’ to 7 ‘very much’)
Activity	21. What am I doing? (just before the alert)	Doing nothing; resting; work; household; self care; caring for partner; active relaxation; passive relaxation; something else
	22. And also?	Doing nothing; resting; work; household; self care; caring for partner; active relaxation; passive relaxation; something else
	23. And…?	Doing nothing; resting; work; household; self care; caring for partner; active relaxation; passive relaxation; something else
	24. I like doing this	7-point scale (1 ‘not at all’ to 7 ‘very much’)
	25. I would rather be doing something else	7-point scale (1 ‘not at all’ to 7 ‘very much’)
	26. This is difficult for me	7-point scale (1 ‘not at all’ to 7 ‘very much’)
	27. I feel I am being active	7-point scale (1 ‘not at all’ to 7 ‘very much’)
	28. I can do this well	7-point scale (1 ‘not at all’ to 7 ‘very much’)

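### The written negative-affect score counts the item on feeling confident in the wrong direction, so the scoring rule contradicts its own stated meaning

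*Protocol article*

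**What the plan says.** Under Instruments, ESM outcome measures, the scoring rule is given in full. It begins "Negative affect will be defined as the mean score of the items" and lists eight items, ending with "I feel desperate’, ‘I feel tensed’, and ‘I feel confident". The score is computed for each completed beep, "with higher scores indicating higher levels of positive and negative affect".

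Two other places confirm that the confidence item belongs to the score:

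- ESM procedure counts "four positive affect and eight negative affect items", and the list reaches eight only with the confidence item included. The Likert items there are rated on a scale "ranging from 1 ‘not at all’ to 7 ‘very much".
- Appendix Table 3 prints "11. I feel confident" under the negative-affect concept (items 5 to 12), with the same anchors as the items on feeling insecure or down.

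No section says that the item is reversed. Study aims counts "a decrease in psychological complaints (depression, anxiety, stress, and momentary negative affect" as evidence of benefit. The ESM part of the statistical analyses fits a linear mixed model with a group-by-time interaction, introduced by "To investigate changes in momentary positive and negative affect between the 3-day ESM baseline and post measurement for each group".

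**The concern.** Seven of the eight items describe unpleasant states, and the eighth describes a pleasant one. Averaging all eight raw values makes greater confidence look like more negative affect, the opposite of what the article says a higher score means. Feeling insecure and feeling confident are near-opposites, yet both add to the total. A caregiver answering 7 and 1 on those two items contributes the same as one answering 1 and 7.

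The abstract lists momentary negative affect among the main outcomes, and the score goes directly into a between-group test. The intervention aims to strengthen caregivers' feelings of competence, so a rise in momentary confidence is plausible. Under the written rule, any such rise would be set against the improvement on the other seven items.

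**Working it through.** **Inputs from the article.** Eight items; plain mean; scale 1 to 7; higher means worse; benefit is a decrease. Counting the listed items (insecure, lonely, anxious, irritated, down, desperate, tensed, confident) gives 8, which reproduces the article's own count.

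**Inputs assumed.** The article gives no item means, standard deviations, correlations or expected changes. Let each of the seven negative items fall by d and confidence rise by c, both as between-group differences in change.

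**Step 1: does the rule agree with its stated direction?** Hold all seven negative items at 1.
- Confidence 7: (7 × 1 + 7)/8 = 14/8 = 1.75.
- Confidence 1: (7 × 1 + 1)/8 = 8/8 = 1.00.

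The fully confident caregiver is recorded as having more negative affect. The best state scores 1.75 instead of 1. The worst state (seven items at 7, confidence 1) scores (49 + 1)/8 = 6.25 instead of 7.

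**Step 2: effect of one point of confidence.** As written, +1/8 = +0.125. With the item recoded as 8 − x, −0.125. The gap is 0.25.

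**Step 3: raw treatment effect.**
- As written: (−7d + c)/8
- Item reversed: (−7d − c)/8
- Item dropped: −d

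| d | c | As written | Reversed | Seven items | Written/reversed |
|---|---|---|---|---|---|
| 0.5 | 0 | −0.4375 | −0.4375 | −0.500 | 100% |
| 0.5 | 0.25 | −0.406 | −0.469 | −0.500 | 87% |
| 0.5 | 0.5 | −0.375 | −0.500 | −0.500 | 75% |
| 0.5 | 1.0 | −0.3125 | −0.5625 | −0.500 | 56% |
| 0.1 | 0.7 | 0.000 | −0.175 | −0.100 | 0% |
| 0 | 0.5 | +0.0625 | −0.0625 | 0.000 | sign reversed |

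Where the negative items improve, the written effect takes the wrong sign only if −7d + c > 0, that is c > 7d.

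**Step 4: standardised treatment effect.** Leaving the item unreversed also shrinks the score's variance. Assume equal item standard deviations and a common inter-item correlation ρ, with the sign changed for pairs that include confidence. The variance of the eight-item sum is then proportional to 8 + 56ρ when reversed and to 8 + 42ρ − 14ρ = 8 + 28ρ as written. At c = d:

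ratio = 0.75 × √[(8 + 56ρ)/(8 + 28ρ)]

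- ρ = 0: 0.75
- ρ = 0.3: 0.75 × √(24.8/16.4) = 0.92
- ρ = 0.5: 0.75 × √(36/22) = 0.96
- ρ = 1: 0.75 × √(64/36) = 1.00

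The standardised loss is therefore 25% at ρ = 0, about 8% at 0.3, about 4% at 0.5 and nil at 1.

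**The case against.** The best defence is that a journal article condenses the full protocol and that item keying is detail usually left to a codebook. The questionnaires elsewhere in Instruments are described by response range, total and direction, without item keys. Table 3 also groups oppositely worded items under self-esteem and physical well-being without marking any reversal, so the missing mark on item 11 is weak evidence on its own. The stated direction of the score could even suggest that recoding was intended, and the item label may be a wording or translation slip.

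Part of this stands. The article cannot show that the raw item will actually be averaged in the analysis. The defence does not rescue the written rule, however. Unlike the established questionnaires, this score is defined here completely, by its items, its arithmetic and its direction, and no outside scoring key is cited for it. Taken together, the three statements are inconsistent. Self-esteem and physical well-being have no composite defined, so the comparison with them concerns only the layout of the table.

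The objections about size also stand. Under-estimation needs a between-group difference in momentary confidence. Caregiving competence, measured by the SSCQ, is a related but different construct, so the aim of raising it does not establish that difference. The 25% is a raw-score figure under equal item changes, and the article gives no item-level data to support any particular scenario.

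**Conclusion.** The scoring rule for momentary negative affect is wrong as written: it contradicts its own stated direction, and this follows from the text without any assumption. The consequence for the treatment effect is conditional. If momentary confidence rises relative to the comparators, the raw benefit is under-estimated, by 25% when all items move equally. The standardised loss is probably nearer 4 to 8%, if inter-item correlations lie between 0.3 and 0.5. If confidence does not differ between groups, reversing the item leaves the raw effect unchanged.

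A reader might infer more than this, and the article does not support it:

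- **That a real benefit will be missed or turned into apparent harm.** Cancellation needs confidence to move seven times as far as each negative item, and reversal needs more than that. Nothing in the article makes this likely.
- **That the trial's main conclusion is at risk.** Table 2 lists the SSCQ and PMS as primary and places momentary negative affect separately under ESM outcomes. The primary analyses, the positive-affect score and the sample size, which rests on the Sense of Competence Questionnaire, are untouched.

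**What to change.** Before group data are examined, state in the ESM outcome definition and in Appendix Table 3 that item 11 is scored as 8 minus the raw value before averaging. If the printed wording is itself the error, correct the wording in both places instead.

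Report the mean of the seven negatively worded items as a sensitivity analysis. The choice of main score should be fixed in advance because the two versions can differ: with d = 0.1 and c = 0.7 they give −0.175 and −0.10.

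The cost is one line in the scoring rule and one in the code. Raw data and data collection do not change. If the team already recodes the item, only the text needs correcting.
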